### Informed consent procedure

Most nursing home patients are incapacitated. In case of incapacity legal, representatives will be asked for informed consent. Capacitated patients will be asked for informed consent themselves. When nursing home staff suspect an UTI, it is not considered practical to obtain written informed consent from the representatives because preferably the blood sample should be drawn as soon as possible. Therefore, informed consent will be obtained pre-emptively at the start of the study or when admitted to the nursing home. This means that patients or their legal representatives provide consent a priori to participate in the study once an UTI is clinically suspected during the study period. This procedure will greatly enhance feasibility of enrolment in psychogeriatric nursing home wards.

### Inclusion and exclusion criteria

Eligible for study participation is elderly nursing home residents clinically suspected of UTI by the attending physician or nurse. Exclusion criteria are suspected respiratory tract infection, suspected other infection requiring antibiotic therapy, previous study inclusion in the past 30 days or lack of written informed consent.

### Study procedures

#### Study enrolment

The study physician will be notified by the nursing home staff when there is potentially eligible patient and will visit the nursing home as soon as possible. The research physician will verify if eligibility criteria are met and will complete study enrolment.

#### Data collection

To meet our post hoc UTI criteria data on signs and symptoms, type and duration of antibiotic used, urine leucocyte esterase, bacterial culture and antimicrobial susceptibility and clinical response are collected. Demographic, clinical and laboratory data are collected through an electronic data capture system using software of Open Data Kit^35^ with which case report forms (CRFs) are designed that incorporate consistency checks to minimise incompatible data points. Data will be handled encoded, working with barcodes scanned by the database APP. Data of paper registration forms are directly entered into online CRFs and uploaded to a predefined database.

Data on culture results (species, susceptibility patterns by minimal inhibitory concentrations) from the laboratory system will be collected in the currently used laboratory systems (Labtrain and Kiestra)

#### Data on signs and symptoms, clinical response and antibiotic use

The attending physician or nurse collects demographic data and data on signs and symptoms of UTI at the day of study enrolment (day 0), see figure 1. The attending physician or nurse will evaluate improvement of signs and symptoms at day 5 and 10 and hospitalisation and/or mortality at day 10. The research physician will visit the nursing homes regularly for monitoring of follow-up. Data on antibiotic use (timing of initial antimicrobial therapy, type of antimicrobial agent and possible switch in antimicrobial therapy) will be collected by the research physician 10 days after study enrolment.

#### Urine sample collection, dipstick analysis and bacterial culture

**Figure 1 F1:**
[figure not shown]
Data collection progress study. *Participants and attending physicians/nurses will not be informed of results (blinded). CRP, C reactive protein; PCT, procalcitonin; POCT, point-of-care testing.

The attending nurse will collect an urine sample for purpose of this study. Urine samples are collected spontaneously voiding either directly in a sterile urine container or in chamber pot (insert pan). When participants have an indwelling urine catheter, urine will be collected when the urine bag is changed. When participants suffer from urinary incontinence or are not able to urinate on the toilet or chamber pot, diapers will be used to obtain urine for bacterial culture and dipstick analysis^36 37^ Urine extraction from diapers can provide a reliable diagnostic specimen, if faecal contamination can reasonably excluded.^38^ Date, time and way of urine collection method are registered by the attending nurse. The urine sample is stored at 4°C.

For dipstick analysis Combur 2 (Roche Diagnostics) will be used (nitrite and leucocyte esterase) by the research physician. Urine will be used for semiquantitative bacterial culture. Inoculation of 10 µL urine to CHROMID CPS Elite (Chromogenic Medium for the immediate identification of *E. coli*, *Proteeae* and *Enterococcus*) agar (Biomerieux) and Columbia Colistin Nalidixin Acid (CNA) agar with 5% sheep blood (Biomerieux) will be streaked using a four quadrant pattern. Bacterial growth will be interpreted after overnight incubation at 35°C in aerobic (CPSE) and CO_2_ enriched (CNA) environment. Uropathogens will be identified by Maldi-tof mass spectrometry (Microflex, Bruker Daltonic). All primary and secondary uropathogens in the European Consensus Guideline are considered as uropathogens in this study. Doubtful isolates are considered as non-uropathogens.^39^ When bacterial growth of ≥10^4^ CFU/mL is found, antibiotic susceptibility testing will be performed using the VITEK2 platform (BioMérieux). Unlike the European Consensus Guideline, for all uropathogens ≥10^4^ CFU/mL growth will be used as cut-off, as urine collection methods will differ and the presence or absence of specific urinary symptoms. Participants, attending physicians and nurses will not be informed of urine dipstick and bacterial culture results (blinded).

#### Blood sample collection and POCT

For POCT, the research physician will collect a blood sample by capillary fingerprick at day 0. Capillary blood sample collection is a preferred collection method in the elderly nursing home population. For CRP testing, the Afinion AS100 POC platform (Alere Health B.V., Tilburg) is used. For PCT testing, the Afias1 PCT Plus (Avant Medical B.V., Geffen) is used.

Both, CRP and PCT platforms enable capillary blood sample collection to better facilitate future implementation in nursing homes. POCT is performed according to the manufacturer’s protocol. For logistic reasons, the POCT is performed centrally at the medical microbiology laboratory of our hospital. POCTs are performed within 4 hours after blood sample collection to ensure stability of CRP and PCT.

Participants, attending physicians and nurses will not be informed of POC test results (blinded).

#### Biological specimen storage and molecular analysis in future

Aliquots of urine samples will be stored (−80°C) when consent is obtained specifically for genetic studies. In future studies metagenomic sequencing will be performed on bacterial DNA, to identify uropathogens and resistance genes.

### Sample size

For the sample size calculation, we used a two-sided p value of 0.05 and a power of 90%. We assume a difference in sensitivity between the two POCTs of at least 10% as clinically relevant. This difference is the net result of discordant test outcomes between the two tests. The magnitude of discordance is the main parameter in the McNemar test used to calculate the sample size for the matched design.

With a proposed sample size of 440 enrolled participants, we are able to adequately assess an increased sensitivity of 10% or more, when the prevalence of UTI in the study population is 40% or more. If the prevalence if UTI is lower, the difference in prevalence that is statistically significant (at the 5%) level increases to 11% or 12%.

Based on data of the national sentinel surveillance network for infectious diseases in nursing homes (SNIV) in 2015, the prevalence of UTI in Dutch nursing homes is 10.3 in 1000 patient weeks. UTI definition by SNIV is broader where response to adequate antibiotic treatment is not taken into account.

In order to reach the target, the PROGRESS study will take place in 13 nursing homes with around 1350 elderly residents in total. Recruitment of a manageable number of approximately 12 participants per week in total is anticipated.

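### The sample size paragraph names the wrong quantity for the 11% and 12% figures and sets no lower prevalence limit; they hold only down to about 27% UTI prevalence

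*Protocol article*

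**What the plan says.** All of the following is in the Sample size section of the protocol article.

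- Error rates: "we used a two-sided p value of 0.05 and a power of 90" per cent.
- Target effect: "We assume a difference in sensitivity between the two POCTs of at least 10% as clinically relevant".
- Method: "The magnitude of discordance is the main parameter in the McNemar test used to calculate the sample size for the matched design". The article gives no value for the discordance.
- Main claim: "With a proposed sample size of 440 enrolled participants, we are able to adequately assess an increased sensitivity of 10% or more", on the condition "when the prevalence of UTI in the study population is 40% or more".
- Fallback claim: "If the prevalence if UTI is lower, the difference in prevalence that is statistically significant (at the 5%) level increases to 11% or 12" per cent. No prevalence is attached to either figure.
- On the surveillance figure of 10.3 per 1000 patient weeks: "UTI definition by SNIV is broader where response to adequate antibiotic treatment is not taken into account".

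The Aim, Outcome, and Data and statistical analysis sections all concern sensitivity, and the two tests are compared by a two-tailed McNemar test. Under Protocol version, amendment 3 adds a design effect of 1.1 for residents who are enrolled more than once.

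**The concern.** The fallback sentence has two faults.

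First, it describes a difference in prevalence that reaches significance. The study compares sensitivities within the same participants, and prevalence enters only through the number of UTI cases available for that comparison. A significance threshold is also not the same as a difference detectable with 90% power: the threshold is the smaller of the two by a wide margin.

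Second, the sentence covers any prevalence below 40% and stops at 12%. The number of UTI cases falls in proportion to prevalence, so the detectable difference cannot stay at 11 or 12 points however low prevalence goes.

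What is at stake is how a non-significant comparison of CRP with PCT will be read. If UTI cases turn out fewer than planned, the paragraph could be cited as showing that a difference of 10 to 12 points would have been found, when power for it may have been well short of 90%.

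**Working it through.** **Inputs.** From the Sample size section: two-sided α = 0.05 (z = 1.96), power 90% (z = 1.2816), difference d = 0.10, 440 enrolled, UTI prevalence 40%. Cases at the design point: 440 × 0.40 = 176. The proportion of discordant pairs, ψ, is not given in the article, so it is solved for.

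**Formula** (McNemar, UTI cases only):

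n = [1.96·√ψ + 1.2816·√(ψ − d²)]² / d²

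**Step 1: reproduce the main claim.** The claim cannot be reproduced from the stated inputs alone. Setting n = 176 and d = 0.10 gives ψ = 0.1715. Check: [1.96 × 0.4141 + 1.2816 × 0.4019]² / 0.01 = 1.3267² / 0.01 ≈ 176. If 440 already contains the design effect, the effective number is 440 / 1.1 = 400, with 160 cases, and ψ = 0.156.

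**Step 2: where 11 and 12 points apply.** With ψ = 0.1715 held constant:

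- d = 0.11: n = [0.8117 + 1.2816·√0.1594]² / 0.0121 ≈ 145, and 145 / 440 = 32.9%.
- d = 0.12: n = [0.8117 + 1.2816·√0.1571]² / 0.0144 ≈ 121, and 121 / 440 = 27.5%.

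**Step 3: below that.** The same equation is solved for d at n = 440 × prevalence. Power for 10 points is Φ([0.10·√n − 1.96·√ψ] / √(ψ − 0.01)).

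| UTI prevalence | UTI cases | Difference detectable with 90% power | Power for 10 points |
|---|---|---|---|
| 40% | 176 | 10.0 points | 90% |
| 32.9% | 145 | 11.0 points | 84% |
| 30% | 132 | 11.5 points | 80% |
| 27.5% | 121 | 12.0 points | 76% |
| 25% | 110 | 12.6 points | 72% |
| 20% | 88 | 14.0 points | 62% |

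**Step 4: sensitivity of the result.** With the design effect (ψ = 0.156, 400 effective participants), 11 and 12 points fall at the same prevalences, 32.9% and 27.5%. Across other common McNemar formulas, with or without the design effect, 12 points is reached between about 26% and 28%. If the smaller discordant cell is held fixed instead of the total ((0.1715 − 0.10) / 2 = 0.036), 12 points is reached sooner, at about 31%.

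**Step 5: significance threshold.** With 176 cases and ψ = 0.1715, the smallest observed difference with p < 0.05 is about 1.96 × √(0.1715 / 176) = 0.061, or 6 points. For 10 points to be the threshold, ψ would have to be about 0.46, since 1.96 × √(0.46 / 176) = 0.100. Power for a true 10-point difference would then be only about 50%, against the stated 90%. The literal wording and the stated power therefore cannot both hold.

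**The case against.** The strongest reply is that this is a drafting slip. The sentence just before it speaks of sensitivity, so few readers will think that prevalences are compared. The values 11% and 12% are right for a moderate shortfall from 40%, and with rounding to whole points 12% stretches to about 25% prevalence. The main claim is openly conditional on prevalence, and the text does say that the difference grows when prevalence is lower.

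Much of that stands, and it rules out three stronger readings that a reader might infer:

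- *That the printed figures are miscalculated.* They are not; they lack the prevalences to which they belong.
- *That prevalence will fall below 27%.* No figure in the article shows this. The five-part definition in Design and setting is strict, and the authors call it stringent in the Discussion, but that gives no number. The surveillance figure is a rate among all residents, not the share of UTI among enrolled suspected cases. The statement in the Introduction that about one third of UTIs are misdiagnosed concerns diagnosed UTI and does not point to a low value either.
- *That discordance exceeds 17% and the study is underpowered.* The 17% is solved backwards from the authors' claim at exactly 40% prevalence. More cases would allow more discordance (about 28% at two-thirds prevalence). The design value may be in the full protocol, and its absence from an article is no fault. The article gives no CRP or PCT sensitivities for nursing home residents from which to judge it.

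The reply does not rescue the sentence as worded. It still names a quantity that is not tested, still confuses significance with power, and still puts no floor under a claim that needs one.

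**Conclusion.** The point holds as a misstatement of a design property. The quantity should be the difference in sensitivity detectable with 90% power, and the 11% and 12% figures are valid only at prevalences of about 33% and 27%. Below about 27% the detectable difference exceeds 12 points. The first part follows from the text and the stated power. The second rests on two assumptions: that the design is just met at 40% prevalence, and that total discordance stays constant as prevalence changes. The 17% discordance (15.6% with the design effect) is a condition of the power claim and not an error that has been shown. The point does not establish that the trial is too small.

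**What to change.** Reword the fallback sentence in the Sample size section:

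- Replace the named quantity with the difference in sensitivity detectable with 90% power.
- Attach the prevalence, or better the number of UTI cases, to each figure. On the back-solved discordance these are about 33% (145 cases) for 11 points and about 27% (121 cases) for 12 points.
- Add that below about 27% the detectable difference is larger than 12 points.
- Compute the final values from the authors' own assumed discordance and their handling of the 1.1 design effect. The 17% used here should not be copied in as a design fact.

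The cost is a few words in one paragraph and a less favourable statement at low prevalence. Enrolment, data collection and the analysis do not change.

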### Data and statistical analysis

The sensitivity of both POCTs to diagnose UTIs defined by the post hoc definition is derived from the optimal point of an ROC. Sensitivities of CRP and PCT tests are compared by a matched analysis approach using a two-tailed McNemar test assessing the statistical significance of differences between the sensitivities of each pair of tests (performed in each study participant).

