### Outcome

The primary outcome is the sensitivity of the POC test to identify patients with a true UTI based on the predefined definition, as derived from receiver operating curves (ROC).

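### McNemar on sensitivity alone, at two separately data-chosen ROC optima, does not show which marker discriminates better, and its false-positive rate can be well above 5%

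*Protocol article*

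**What the plan says.** Under *Data and statistical analysis* the protocol article fixes two steps. First: "The sensitivity of both POCTs to diagnose UTIs defined by the post hoc definition is derived from the optimal point of an ROC". Second, the two sensitivities are compared by a "two-tailed McNemar test assessing the statistical significance of differences between the sensitivities of each pair of tests".

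*Outcome* makes sensitivity the primary measure: "The primary outcome is the sensitivity of the POC test to identify patients with a true UTI". Specificity is not part of it, and nothing in the article fixes, matches or compares specificity between the tests.

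The cut-offs come from the study's own data. The Introduction's section on CRP and PCT says that cut-offs must be determined in this population, and the *Discussion* says that the values found will need confirmation in later trials. The rule that defines the optimal point is not named.

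*Sample size* is built on the same comparison: two-sided 5%, 90% power, and "We assume a difference in sensitivity between the two POCTs of at least 10% as clinically relevant".

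**The concern.** There are two separate faults.

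1. **Specificity is free.** McNemar on the UTI cases counts only those positive on one test and negative on the other. A marker whose optimum falls at a lower threshold gains sensitivity and loses specificity, and the test sees only the gain. Two markers with the same ROC curve, read at different points on it, can differ significantly.

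2. **The cut-offs are estimated but treated as fixed.** McNemar's null variance covers the sampling of patients at given thresholds. Here each threshold is chosen separately from the same participants, and that extra variation is not in the test.

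At stake is the only formal comparison that the article describes, and the one for which the study was sized. The stated purpose is to spare antibiotics in residents who do not need them, so specificity given up for sensitivity works against that purpose.

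**Working it through.** **Inputs from *Sample size*.** Two-sided alpha 0.05, power 90%, difference d = 0.10, N = 440, prevalence 40%. This gives 440 × 0.40 = 176 UTI cases and 264 non-cases. The discordance ψ, which the article calls the main parameter, is not given there.

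**The plan's own figure.** With the usual McNemar formula (Connor), n = (z_α√ψ + z_β√(ψ − d²))² / d². For ψ = 0.17: (1.960 × 0.4123 + 1.2816 × 0.4000)² / 0.01 = 174.4 cases, and 174.4 / 0.40 = 436. So 440 is attainable. Back-solving gives ψ of about 0.171, or about 0.156 with the design effect of 1.1 from the amendment list. Without a stated ψ the figure cannot be independently confirmed. The calculation treats CRP and PCT as two fixed binary tests.

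**Simulation under equal markers.** Assumptions not in the article: binormal markers with identical ROC curves, AUC 0.6-0.9, and a range of within-person correlations. Each marker's cut-off is its own empirical optimum, by Youden or by closest-to-corner. McNemar is then run in the UTI cases. The table shows exact McNemar rejection at nominal 5%, 40% prevalence, correlation 0-0.8, 2,000 trials per cell:

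| AUC | Youden | Closest-to-corner |
|---|---|---|
| 0.6 | 60-69% | 18.5-33% |
| 0.7 | 44-58% | 11-26% |
| 0.8 | 34-46% | 9-19% |
| 0.9 | 23-35% | 4.6-11% |

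A separate run with correlation limited to 0-0.6 gives about 21-66% (Youden) and about 5-25% (closest-to-corner). In that run, chance gaps of 10 points or more arise in about 12-63% and about 1-24% of trials respectively. With cut-offs fixed in advance, exact McNemar rejects in about 2-5%, so choosing cut-offs from the data is the cause.

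**Why, by hand.** Take AUC 0.8, correlation 0.5.
- *Youden.* Simulated discordance is 0.273. McNemar's null standard error is √(0.273/176) = 0.039, which implies a mean absolute difference of 0.798 × 0.039 = 0.031. The simulated value is 0.075, or 2.4 times as large. A normal difference with 2.4 times the assumed spread exceeds 1.96 assumed standard errors in about 41% of trials. The simulation gave 39% (exact) and 43% (asymptotic).
- *Closest-to-corner.* Discordance is 0.270, the implied mean difference is again 0.031, and the simulated value is 0.042, or about 1.3 times. This predicts about 14%. The simulation gave 11% and 13%.

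**Direction of the false positives.** Under Youden, in 96-100% of rejections (correlation 0-0.6) the marker with the higher sensitivity had the lower specificity. The test is mostly picking up different positions on the same curve.

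**Checks of alternatives under the same null.**
- Paired DeLong AUC test: 4.3-5.5%.
- Sensitivity at a common specificity of 0.70, with a participant-level bootstrap that re-derives the cut-offs: 3.0-4.6%.
- Plain McNemar at an empirically matched 80% specificity: 7.6-13.0%, still inflated.

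**The case against.** **The optimum rule is not named, and a full analysis plan may name it.** This stands, and it limits the size. A reader might infer that the error rate is far above 5% whatever rule is used. The article does not support that: under closest-to-corner the inflation is moderate, and at AUC about 0.9 it can be near nominal. The stated method remains a problem all the same, because an analysis plan would have to replace the comparison and not merely complete it.

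**The question is sensitivity, not overall discrimination.** This stands in part. When McNemar rejects, the true sensitivities at the two selected cut-offs usually do differ in the same direction (95-100% of rejections in one set of simulations). The error is therefore in reading the result as evidence that one marker is better. It does not help that the cut-offs are unstable: such a difference would not be expected to repeat.

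**The aim and primary outcome concern each test's own sensitivity.** This is correct. A reader might infer that the primary estimates are invalid too. The McNemar problem does not show that. The comparison nevertheless appears in *Design and setting*, drives *Sample size*, and is the only test described.

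**An ROC optimum already weighs specificity, and the cut-offs will be confirmed later.** The first is normally true of how a cut-off is chosen, but the comparison still ignores specificity. The second limits direct harm, since the *Discussion* expects further trials, but it does not correct this study's p value.

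**Conclusion.** Wrong as written. McNemar on sensitivity alone, with each marker at its own data-chosen optimum and specificity free, does not establish which marker discriminates better. For two equally good markers its false-positive rate can be well above 5%.

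The cause does not depend on the simulation settings, but the size does. It rests on the unnamed optimum rule and on assumed binormal markers, AUC and correlation, none of which the article gives. The inflation is large in every Youden scenario examined. With closest-to-corner it is moderate at modest AUCs and can vanish at high AUC. The plan's own 10-point threshold of clinical relevance gives limited protection: chance gaps of that size are common under Youden and occur in up to about a quarter of trials under closest-to-corner.

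**What to change.** Before analysis, replace the McNemar comparison at separate ROC optima with one of the following:

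- **(a)** the paired (DeLong) comparison of AUCs; or
- **(b)** the difference in sensitivity at one common specificity named in advance, with confidence interval and p value from a participant-level bootstrap that re-derives both cut-offs in each resample. Matching specificity in the data and keeping plain McNemar is not enough.

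Keep McNemar only for cut-offs set in advance. Report every ROC-optimum sensitivity together with its specificity.

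**Cost.** A change of analysis wording and a short program, with no new data. The nominal p value is likely to be less favourable. Option (b) requires the common specificity to be chosen and justified beforehand. The power statement for 440 was derived for McNemar on fixed tests and should be restated for the test adopted.

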### Protocol version

4 March 2019, v.5.

1 September 2017 original 21 October 2017 amendment 1: Addition of information brochures for nursing home staff and patients.

20 November 2017 amendment 2: Change of nomenclature for part of nursing home residents to temporary rehabilitation patients (at rehabilitation wards).

7 March 2018 amendment 3: Change exclusion criterion prior inclusion to prior inclusion in the past 30 days. Subsequently to account for non-independence of observation for a limited number of participants, the sample size is adjusted with a design effect of 1.1.

28 June 2018 amendment 4: (1) change in blood sample collection method (venipuncture to finger prick collection) due to availability of new PCT POCT with small input volume, as fingerprick blood sample collection is a preferred collection method in the elderly nursing home population, (2) change sample size retaining stringent criteria (p=value 0.05 and power 90%), (3) prolongation study duration: 12–18 months and (4) expansion of number of nursing homes from 11 to 12 nursing homes.

3 March 2019 amendment 5: (1) expansion of number of nursing homes from 12 to 13 nursing homes, (2) adjusted informed consent procedure for capacitated residents.

1 July 2019 amendment 6: (1) expansion of number of nursing homes from 13 to 14 nursing homes and (2) addition of post hoc analysis using different UTI definitions.

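### Repeat inclusion of residents is recognised in the sample size (design effect 1.1) but not in the planned McNemar test, which treats every pair as independent; the effect on the p value is modest.

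*Protocol article*

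**What the plan says.** - **Inclusion and exclusion criteria.** The bar on re-entry is limited to "previous study inclusion in the past 30 days". A resident with a new suspected UTI after that interval may be enrolled again.
- **Protocol version, amendment 3.** This amendment introduced the 30-day rule and gives its statistical consequence: "to account for non-independence of observation for a limited number of participants, the sample size is adjusted with a design effect of 1.1".
- **Sample size.** The inputs are "we used a two-sided p value of 0.05 and a power of 90" per cent, and for the effect, "We assume a difference in sensitivity between the two POCTs of at least 10% as clinically relevant". The target is given as "With a proposed sample size of 440 enrolled participants", adequate "when the prevalence of UTI in the study population is 40% or more". This section mentions no design effect.
- **Data and statistical analysis.** The sensitivities are "compared by a matched analysis approach using a two-tailed McNemar test". The pair is described as the two tests in each participant, and nothing is said about participants with more than one pair.
- **Design and setting.** Matching means CRP and PCT measured in the same person, and nothing more.

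**The concern.** McNemar's test deals with one correlation, that between the CRP and PCT results within a pair. It assumes that the pairs themselves are independent. Once a resident can return, the unit of analysis is the episode, and two episodes from one resident may share whatever makes one marker outperform the other in that person.

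The investigators saw this and acted on it in the sizing only. The two steps do different jobs. Enlarging the sample restores information lost to correlation, and so protects power. It does not change the variance that the test uses. If the correlation is positive, that variance is too small at any sample size, and the test of the primary comparison rejects more often than its stated 5%.

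**Working it through.** **1. The plan's own figure.** Inputs from Sample size: two-sided alpha 0.05, power 90%, difference d = 0.10, 440 enrolled, UTI prevalence 40%. Only residents with UTI count towards sensitivity: 440 × 0.40 = 176.

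The usual McNemar formula is n = (1.96√ψ + 1.2816√(ψ − d²))² / d², where ψ is the proportion of discordant pairs. The article says of this quantity: "The magnitude of discordance is the main parameter in the McNemar test used to calculate the sample size for the matched design". It gives no value, so 440 cannot be reproduced directly. Solving backwards:

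| Reading of 440 | Effective UTI cases | ψ implied |
|---|---|---|
| No design effect included | 176 | 0.172 |
| Design effect 1.1 included | 176 / 1.1 = 160 | 0.156 |

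Both are credible. ψ = 0.17 gives 437 enrolled without inflation; ψ = 0.155 gives 397, and 397 × 1.1 = 437. Amendment 4 changed the sample size after amendment 3 introduced the 1.1, so the article does not show whether 440 still contains it. If it does not, and ψ = 0.17, power is 90.3% with independent pairs and 87.3% at a design effect of 1.1.

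**2. Effect on the test.** Let DE be the true variance divided by the variance that the plain test assumes.

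- Assumed SE / true SE = 1/√DE = 1/√1.1 = 0.953, so the SE is about 4.7% too small.
- Critical value on the true scale: 1.96/√1.1 = 1.869.
- Two-sided error: 2 × (1 − Φ(1.869)) = 0.0617.

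For neighbouring values, DE 1.05 gives 0.0558 and DE 1.2 gives 0.0736. The sample size does not enter, so enlarging it does not help.

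**3. What DE could be.** If no resident has more than two UTI episodes, a share r of episodes are second episodes, and the CRP-PCT difference has within-resident correlation ρ, then DE = 1 + 2rρ. Neither r nor ρ is in the article; the ranges below are assumptions.

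| r | ρ = 0.25 | ρ = 0.5 | ρ = 1 |
|---|---|---|---|
| 5% | 1.025 | 1.05 | 1.1 |
| 10% | 1.05 | 1.1 | 1.2 |
| 20% | 1.1 | 1.2 | 1.4 |

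**4. Check by simulation.** 40,000 runs under no difference in sensitivity, 176 pairs, ψ = 0.155:

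| r, ρ | Plain McNemar rejects | Resident-clustered version rejects |
|---|---|---|
| No repeats | 5.2% | 5.2% |
| 10%, 0.5 (DE 1.1) | 6.6% | 5.3% |
| 10%, 1 (DE 1.2) | 7.8% | 5.1% |
| 20%, 0.5 (DE 1.2) | 7.7% | 5.0% |

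The excess over the no-repeat baseline at DE 1.1 is 6.6 − 5.2 = 1.4 points, close to the 1.2 points from the formula (6.2 − 5.0). The clustered version removes it.

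**The case against.** - **The article is condensed, and handling of a few repeats belongs in an analysis plan.** The Discussion does refer to a data analysis plan that is not shown, and that plan may already deal with this. But the article is not silent: it names the test for its main comparison, and that test does not fit the enrolment rule. The point is about the choice stated.
- **The 1.1 stands only in the amendment history.** True, and it may not survive in 440. The point does not depend on that. The 30-day rule is current text, and it is enough to make a plain McNemar test unsuitable. The history supplies the investigators' own acknowledgement and a figure for the size.
- **Few pairs are affected.** This has force. A resident contributes dependent pairs only through two or more episodes that each meet all five criteria for true UTI, and the protocol itself speaks of a limited number of people. The design effect among those episodes could be below 1.1. With zero correlation there is no inflation, and with negative correlation the test would be conservative.
- **A stronger reading about nursing homes.** A reader might infer that the sample was also inflated for clustering in homes, or that home effects make the error much larger. The article supports neither: the 1.1 is tied to repeat inclusion alone. With 176/13 = 13.5 UTI cases per home and DE = 1 + (13.5 − 1) × ICC, assumed ICCs of 0.01, 0.02 and 0.05 would give errors of 6.5%, 8.0% and 12.4%. No such ICC is documented. Home influences that shift both markers alike largely cancel within the pair; only variation between homes in the CRP-PCT difference would count.
- **A stronger reading about intervals.** A reader might extend the criticism to confidence intervals or a bootstrap. The analysis section describes neither, so there is nothing stated to correct.

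**Conclusion.** The mismatch is real: the protocol permits repeat inclusion, calls the resulting observations non-independent, adjusts the sample size, and then names a test that assumes independence. The consequence is modest. At a design effect of 1.1 the standard error is about 4.7% too small and the two-sided error about 6.2% instead of 5%. Those figures are conditional on 1.1 being the true variance ratio among UTI-positive episodes, which needs positive within-resident correlation of the CRP-PCT difference. The protocol's own allowance presumes such correlation but does not establish it. The matter deserves correction because it touches the primary comparison and is easily repaired, not because it would be likely to overturn a clear result.

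**What to change.** In Data and statistical analysis, replace the plain McNemar test with a paired test clustered on resident: the Obuchowski or Durkalski version of McNemar's test, or a GEE on the paired results with robust errors clustered on resident. Add a sensitivity analysis restricted to each resident's first inclusion. In Sample size, state the discordant proportion assumed and whether 440 includes the 1.1.

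Clustering on nursing home may be added as a secondary check. With only 13 homes (14 after the last amendment listed) its variance estimate would be imprecise, so it should not be the main analysis.

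The cost is one or two sentences and standard software, with no new data and no change in trial conduct. The downside is slightly less favourable p values, and fewer episodes in the first-inclusion analysis.
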